**Figure 3 F3:**
[figure not shown]
Example of the impact exposure data generated by the MAREC. The above example shows the time (400 s) on the x-axis. On the left y-axis is acceleration measured in *g*=9.81 m/s^2^, with red for the operator and blue for the boat hull, and on the right y-axis is the boat speed measured in knots shown by the green line. SOG, speed over ground.

**Figure 4 F4:**
[figure not shown]
Flow of exposure data and pain data. All agencies will have access to the exposure data they have submitted to the MultiAgency, prospective, exploratory, non-intervention, cohort Study on Human Impact Exposure oNboard high-speed boats (MASHIEN) Database and to the anonymised pain data from their units. Agencies wishing to also save anonymised pain data locally may set up local databases for this purpose. GPS, Global Positioning System. MAREC SW, MAREC accelerometer recorder software.

#### Sea state and meteorological data

Data will be collected on weather and sea state from meteorological sources as these factors affect the amount of slamming. Oceanographical data (sea state) and meteorological data (wind, temperature, rain) will be extracted from global meteorological databases. Even the characteristics of the boat type used will be registered while mounting the device onboard.^11^

#### Health and working conditions survey

A validated web-based questionnaire for surveying the health and working conditions of high-performance marine craft populations will be designed to assess a range of factors, including musculoskeletal injuries, noise exposure, psychological stress and fatigue.^12^

### Target sample size

A recent systematic review of five studies reported 1.1 injuries per person per year serving as high-speed boat operators.^5^ Our study follows operators for at least 2 months, estimating that one of six operators may experience one acute episode with musculoskeletal injury. The Minimally Clinically Important Difference for back pain VAS is 14 mm, and the SD is 20 mm.^27^ Consequently, a minimum number of 192 participants would be necessary to reach 80% power (1 minus type II error probability) at a 0.05 significance level (type I error probability) if followed for 2 months.

### Statistical methods

We will report descriptive statistics and calculate the mean, SD and range for human impact exposure and pain scores. Peak acceleration values, m/s^2^, will be registered in all three axes, x, y and z. A data analysis engine will categorise impacts with various combinations of the impact characteristics and allow for calculating correlations to registered pain experiences and various variables of the reported pain. We will use Pearson correlation coefficients to examine the association between human impact exposure and pain scores. We will also use linear regression to examine these associations while controlling for potential confounding variables (eg, age, sex, body mass index). Multivariate analysis based on analysis of variance (ANOVA) and logit models will be used to identify which characteristics of the impacts correlate to reported pain of various intensities, locations and durations after exposure. The results of the statistical analysis are expected to indicate which impact characteristics show a correlation to reported experiences of pain. Based on these findings, we will establish which impact exposure levels and characteristics are safe regarding physical and cognitive capabilities.

This analysis can also validate alternative ways of quantifying human exposure to discrete whole-body impacts and their potential relevance for predicting the risk of injury. Candidates for alternative units include calculated kinetic energy transferred or absorbed, J/kg, and the speed of this transfer, mechanical power, J/(kg·s). The analysis may need to include the calculated total change of speed and the distance during which the retardation of the boats and the human bodies occurs in each impact.

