Despite these limitations, this study represents a significant step forward in understanding the occupational hazards associated with high-speed boat operations. Its findings can inform evidence-based guidelines for injury prevention, contribute to safer operational practices and support improvements in boat design and suspension technology. Data on what magnitudes and characteristics of impacts correlate to reported pain can indicate what levels and types of exposure are potentially harmful. This knowledge can be used to suggest limits for impact exposure during training.

The exposure results can help validate the scope and the severity of this problem and assess if preventive measures are needed or justified. The availability of these data can help establish the clinical and economic burden of these injuries and inform decision-makers regarding resource allocation, compensation and other relevant issues. Finally, the results can guide the development of evidence-based guidelines and standards for the safe operation of high-speed boats. This can reduce the risk of injuries and promote the health and well-being of high-speed boat operators.

Based on the data generated by this study, dashboard instruments can be calibrated for each type of boat to give boat operators continuous real-time information about when hull impacts rise to dangerous levels. Such devices need only a single three-axis hull accelerometer and a visual display.^31^ Additional research can be aimed at demonstrating the effectiveness of this type of device in real-world use and operations. Further research will investigate whether the results of this study are transferable to human impact exposure in all-terrain vehicles^32 33^ and could identify occupationally relevant exposure limits for off-road and all-terrain vehicles.

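### Statistical methods commits to declaring exposure levels safe directly from an exploratory correlation screen, with no check before that conclusion and against the article's own caveats

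*Protocol article*

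**What the plan says.** All places are in the protocol article.

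**Statistical methods.** After descriptive statistics, "A data analysis engine will categorise impacts with various combinations of the impact characteristics and allow for calculating correlations to registered pain experiences", and also to further aspects of the pain record. Pearson correlations, linear regression with confounder adjustment, ANOVA-based multivariate analysis and logit models then pick out the impact characteristics that go with pain of differing strength, site and persistence. The paragraph ends with a commitment: "Based on these findings, we will establish which impact exposure levels and characteristics are safe regarding physical and cognitive capabilities". The next paragraph adds alternative exposure units based on energy and power, and says that the same analysis can serve to validate them.

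**Size of the screen.** Exposure to impacts lists seven characteristics (number, peak level, rise time, vector sum, three-dimensional direction, duration, jerk) over nine channels. The Pain section lists four pain variables (intensity, duration, location, modality). Subgroup analysis adds an open list of subgroups.

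**Target sample size.** "The Minimally Clinically Important Difference for back pain VAS is 14 mm, and the SD is 20 mm", "estimating that one of six operators may experience one acute episode with musculoskeletal injury", and "a minimum number of 192 participants would be necessary to reach 80% power" "at a 0.05 significance level (type I error probability) if followed for 2 months".

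**Caveats elsewhere.** The Abstract expands the study name with the word exploratory. The strengths and limitations list and the Discussion both say that the design cannot settle cause and effect and that interventional work must follow. The Discussion leaves refinement of thresholds to future research and, on limits, says only: "This knowledge can be used to suggest limits for impact exposure during training".

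**The concern.** The label exploratory covers generating hypotheses. It does not cover declaring a level of exposure safe on the data that suggested it. Two errors follow from the step as written.

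- **Overstatement.** Characteristics and levels are chosen because they are strongly associated with pain in this sample. Chosen that way, their strength in the same sample is biased upward, whatever the selection rule.
- **False reassurance.** The sentence sorts characteristics into safe and not safe according to whether a correlation appears. A characteristic whose effect the study could not detect would then fall on the safe side. For operators this is the more serious error.

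The sentence also promises more than the article elsewhere says the design can deliver, so a reader cannot tell which of the two statements the final report will follow.

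**Working it through.** **1. Reproduce the sample size.** Inputs from Target sample size: difference 14 mm, SD 20 mm, power 80%, significance level 0.05 (two-sided assumed; sidedness is not stated), one in six operators with an injury episode.

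- Per group, normal approximation: 2 × (20 × (1.960 + 0.842) / 14)² = 32.04, taken as 32.
- Divide by the injury proportion: 32 / (1/6) = 192, the stated figure. One-sided testing would give 26 × 6 = 156, which does not match.
- The one in six agrees with the cited rate of 1.1 injuries per person-year over two months: 1 − exp(−1.1 × 2/12) = 0.168.

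So 192 provides for a single contrast in back pain VAS, with 192 / 6 = 32 expected injury episodes. It was not derived to show that any impact characteristic is harmless.

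**2. What a null correlation would mean.** Illustration, assuming one exposure summary and one pain summary per participant, 192 participants and two-sided 0.05, by Fisher's transformation:

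- Correlation detectable with 80% power: tanh((1.960 + 0.842) / √189) = 0.20.
- Smallest observed correlation that reaches 0.05: tanh(1.960 / √189) = 0.14.

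By the same formula, an observed correlation of zero has a 95% interval of about −0.14 to +0.14. A true correlation near 0.14 would be missed about half the time. Conversely, weaker true correlations selected at that level would appear only in inflated form. Daily logs and clustering by boat and centre would change these figures; the point is that absence of detection leaves a range of non-zero effects open.

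**3. Chance findings, illustration only.** The article states neither the number of tests nor a level for the screen. Assume 7 characteristics × 4 pain variables = 28 tests, each at 0.05, with no true association anywhere.

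- Expected false positives: 28 × 0.05 = 1.4, whatever the correlation between tests.
- Chance of at least one if independent: 1 − 0.95²⁸ = 76%.
- With a common correlation between tests of 0.3, 0.5 or 0.8 (simulation of correlated normal statistics): 64%, 49% or 25%.

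Combinations of characteristics, channels and subgroups would add tests.

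**4. Set the statements side by side.**

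| Place | Claim |
|---|---|
| Statistical methods | Safe levels and characteristics will be established from the correlations |
| Strengths and limitations list; Discussion | Cause and effect cannot be settled; later interventional work is needed |
| Discussion | Thresholds are to be refined by future research; the data can help to suggest limits |

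The first row cannot stand beside the other two. The later research is mentioned, but not as a condition for calling a level safe.

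**The case against.** The strongest reply is that this is one sentence firmer than its surroundings in an article that calls the study exploratory, and that much of what looks absent may be in a full protocol or analysis plan that is not shown. A good part of that stands, and it rules out several stronger readings.

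- **That the screen is run at 0.05.** A reader might infer this because "at a 0.05 significance level" is the only level in the article. It belongs to the sample-size calculation; Statistical methods gives no test level and no significance-based selection rule.
- **That a definite number of false positives is built in.** The article fixes no number of tests, and the 1.4 above assumes that nothing is related to pain, which runs against the injury evidence in the Introduction. The tests are also correlated: jerk is built from peak and rise time, and the vector sum from the three axes.
- **That there is no primary exposure-pain pair or multiplicity rule.** An article commonly leaves these to the full documents, so their absence here shows nothing.
- **That training limits and dashboard settings will follow directly.** These appear only in the Discussion and in conditional terms.

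A tighter error rate across the screen would also not be a clean remedy, because it makes missed associations more frequent. At 32 per group, a Bonferroni level for 28 tests lowers power for the 14 mm contrast from 80% to 37%. False-discovery-rate control pushes in the same direction.

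What does not fall is the step that is written down. An unseen analysis plan may add detail, but it does not remove the commitment to establish what is safe from these correlations, or its conflict with the article's own limitations.

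**Conclusion.** The point holds as a fault in the stated conclusion. Statistical methods moves from an open-ended screen to a declaration of safe exposure levels and characteristics, on the same data, with no check placed in between, and this contradicts the caveats in the strengths and limitations list and the Discussion.

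The firm part rests on the text and on the reproduced sample size: 192 covers one 14 mm VAS contrast with about 32 expected injury episodes. Failure to find a correlation for one of many characteristics is therefore weak evidence of safety. The size of the false-positive problem is illustrative only: 1.4 expected and a 25–76% chance of at least one, under the assumed 28 tests, the assumed 0.05 and a global null. The conclusion does not depend on that count.

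The wording should be corrected before analysis. Inclusion is expected to close before 30 June 2027, so this can still be specified in advance.

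**What to change.** 1. **Reword the conclusion.** Replace the commitment to establish safe levels with a statement that the analysis will identify candidate exposure levels associated with reported pain. This brings Statistical methods into line with the limitations and the Discussion.
2. **Check each candidate level outside the data that produced it.** Derive it with one centre left out, and report its performance in that centre with confidence intervals. Repeat over centres. The number and size of centres are not given, so allow small centres to be grouped.
3. **Rule out the inference from silence.** State that the absence of a detected correlation is not evidence of safety, and report the confidence interval for every such characteristic.

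No new data are needed. The cost is a less definite conclusion and some extra computing. The article describes both a shared study database and data remaining with the centres, so the plan should say how the left-out-centre check will be run across them.

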## Methods and analysis

### Study design, setting and participants

This prospective, self-controlled, non-intervention, multicentre cohort study investigates the acute effects of slamming-induced impact exposure on high-speed boat operators’ musculoskeletal systems and cognitive functions. The study protocol is reported according to Strengthening the Reporting of Observational Studies in Epidemiology guidelines and was registered prospectively on ClinicalTrials.gov with the identifier NCT05299736.^22^ This study has been designed by the North Atlantic Treaty Organization (NATO) Science & Technology Organization, Research Task Group HFM-344. The recruitment of academic centres started in 2022 and the first participant was enrolled on 23 August 2024. We expect to close the inclusion of study participants before 30 June 2027. The schedule of participant enrolment, exposures and assessments is presented in table 1.

**Table 1 T1:** Schedule of enrolment, exposures and assessments

Timepoint	Study period							
	Enrolment	Allocation	Post allocation					Close-out
	*−t_1_*	0	*t_1_*	*t_2_*	*t_3_*	*t_4_*	*etc*	*t_90_*
Enrolment:								
Eligibility screen	X							
Informed consent	X							
Allocation		X						
Exposure:								
Slamming forces								
Whole body impacts								
Assessments:								
Questionnaire		X						X
Level of pain (VAS)		X	X	X	X	X	X	X
Pain character (pain drawing)		X	X	X	X	X	X	X

Timepoints *t* define days 1–90.

VAS, Visual Analogue Scale.

Eligible participants are military and civilian agencies, organisations and institutions that operate boats capable of hydroplaning speeds, have professional high-speed boat operators and allow the installation of accelerometer devices and data recording. The study will include operators in each centre between age 18 and 65 years who either operate or are being regularly transported onboard high-speed boats and have signed the informed consent form.

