### Outcomes, data sources and measurements

#### Pain

Pain is a common symptom experienced by high-speed boat operators exposed to repeated slamming impacts, and it is a common reason that operators seek medical attention or modify their work activities.^1^ By studying the occurrence and duration of pain and its correlation in time after slamming-induced impacts, the study aims to assess the risks of injurious exposure. Pain can be monitored non-invasively using validated methods, such as the Visual Analogue Scale (VAS) or Numeric Rating Scale, which rate pain intensity, and pain drawings to assess pain location, duration and interference with activities.

In this study, self-reported pain will be logged daily through a smartphone application, PainDrawing (figure 1),^23^ adapted specifically for this project.^24^ The application is based on the Nordic Minister Council’s pain drawing form and a VAS. PainDrawing can be downloaded freely from Google Play and Apple AppStore and works offline and in flight mode. Reported pain data will comprise the following characteristics: location, pain modality, intensity and duration. Participants will be urged to log pain daily for the whole test period, regardless of whether they have been on board a boat or not. Participants will serve as their own controls by comparing periods of exposure onboard with periods of not working onboard.

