#### Exposure to impacts

A data logger system (MAREC, Research Electronics AB, Siljansnäs, Sweden) was designed specifically for this study. The device comprises three triaxial micro-electromechanical system (MEMS) accelerometers with a range of ±25*g*, a Global Positioning System antenna for tracking speed, and a data logger unit with 10 digital channels (figure 2). The acceleration data are recorded at a sampling rate of 600 Hz and stored on an internal removable 16 GB USB memory stick. One accelerometer fitted to the hull will record hull accelerations. Two accelerometers fitted in kidney belts, as depicted in figure 2, will be worn by two operators, normally the coxswain and the navigator.^11^

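### The named analyses (Pearson correlation, covariate-adjusted regression, ANOVA, logit) do not, as named, make the own-control comparison that the design promises or allow for repeated daily records per person

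*Protocol article*

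**What the plan says.** The design sections of the protocol article are clear about the comparison intended. Under Study design, setting and participants: "This prospective, self-controlled, non-intervention, multicentre cohort study investigates the acute effects of slamming-induced impact exposure". Under Pain: "Participants will serve as their own controls by comparing periods of exposure onboard with periods of not working onboard". Outcome data are repeated: "self-reported pain will be logged daily through a smartphone application", and "Participants will be urged to log pain daily for the whole test period, regardless of whether they have been on board a boat or not". The time points in Table 1 "define days 1–90", and the sample size section gives a minimum follow-up of two months. Exposure is partly shared. Under Exposure to impacts, each boat carries one hull sensor and "Two accelerometers fitted in kidney belts", worn by two operators.

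The Statistical methods section then says "We will use Pearson correlation coefficients to examine the association between human impact exposure and pain scores". It adds linear regression "controlling for potential confounding variables (eg, age, sex, body mass index") and a multivariable step using ANOVA and logit models. The article mentions no participant effect, repeated-measures or conditional model, cluster-robust standard error, or clustering by boat or centre. The same section intends to derive safe exposure levels from the results.

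**The concern.** The design and the analysis answer different questions. A self-controlled study asks whether a person hurts more after their own exposed days than after their own unexposed days. In standard form, the named methods ask whether records (or people) with more exposure show more pain.

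The example covariates point the same way. Age, sex and body mass index are constant, or nearly so, over two to three months. A within-person contrast removes them, so listing them suggests a pooled or between-person model.

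Either unit of analysis causes trouble. If daily records are pooled, repeated records from one person are treated as separate evidence, and the slope blends the acute effect with stable differences between people. If each person is reduced to one value, the own-control information is lost. Because exposure limits are meant to follow from these results, both false precision and a blended slope would carry through to them.

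**Working it through.** **Inputs from the article.** Minimum follow-up is two months, so about 60 daily records; the schedule runs to 90. The compliance threshold of 24 days per month gives 2 × 24 = 48 records in two months. The planned sample is 192. The article gives no ICC for pain or exposure, so the ICCs below are assumptions, shown as ranges.

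**The plan's own figure.** The article gives a difference of 14 mm, an SD of 20 mm, 80% power and a 0.05 level. It states neither the formula nor the sidedness. A two-sided comparison of two independent groups gives n per group = 2 × (20 × (1.960 + 0.8416) / 14)² = 32.04. Multiplied by 6 (one operator in six expected to have an episode), this is 192.2, which reproduces 192. The paired version, (20 × 2.8016 / 14)² = 16.02, times 6, gives 96 and does not. The sample size is therefore consistent with an independent-groups calculation rather than a within-person one.

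**Standard error of a pooled slope.** With m records per person, exchangeable clustering and no true effect, the true SE divided by the naive SE is √(1 + (m − 1) × ICC_exposure × ICC_pain). The actual size of a nominal 5% test is 2 × (1 − Φ(1.96 / factor)). For m = 60 and ICC_pain = 0.3:

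| ICC_exposure | 1 + 59 × ICC_exposure × 0.3 | SE factor | Actual type I error |
|---|---|---|---|
| 0.05 | 1.89 | 1.37 | 15% |
| 0.2 | 4.54 | 2.13 | 36% |
| 0.5 | 9.85 | 3.14 | 53% |

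Over m = 48 to 90, ICC_pain 0.1 to 0.5 and ICC_exposure 0.05 to 0.5, the factor runs from 1.11 to 4.82 and the type I error from 8% to 68%.

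**Check by simulation** (192 people × 60 days, 1,000 runs per setting, ICC_pain 0.3). The pooled test rejected a true null in 15%, 34% and 50% of runs at the three exposure ICCs. A test on person-centred data rejected in about 5% each time.

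**Where there is no inflation.** At ICC_exposure = 0 the factor is 1. In simulation at ICC_pain = 0.5 the pooled test rejected in 4.6% of runs. It was only less efficient: the SD of the slope was 0.0093, against 0.0066 within person.

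**Mixing of slopes.** A pooled slope is approximately ICC_exposure × between-person slope + (1 − ICC_exposure) × within-person slope. With ICC_exposure = 0.3, within-person slope +0.20 and between-person slope −0.20, this is 0.3 × (−0.20) + 0.7 × 0.20 = 0.08. The simulation gave 0.08 pooled and 0.20 within person. With both slopes at 0.20, the pooled slope was 0.20.

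**The case against.** The article never states the unit of analysis. Linear regression, ANOVA and logit are families that include participant fixed effects, repeated-measures ANOVA and conditional logit, and a full analysis plan that is not shown could specify them. The covariates are only examples. The section on bias and confounding names pre-existing conditions, collects baseline health, logs activities outside work and commits to adjustment. The study is labelled exploratory and disclaims causal proof.

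Much of this stands, and it limits the point. A reader might infer that the p-values and confidence intervals are bound to be far too optimistic. The article does not support that: inflation requires daily records to be pooled and exposure to cluster by person, and its size depends on ICCs that are not given. A reader might also infer that the pooled slope would have the wrong sign. That too depends on inputs the article lacks, and mixing arises only if the two slopes differ. Shared boats could add further dependence, but the article does not say whether crews are fixed, so no figure is put on it.

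The objection does not remove the mismatch. The section names its methods and example covariates, and nothing there carries over the own-control comparison. Adjusting for measured confounders neither accounts for repeated records nor isolates the within-person effect.

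**Conclusion.** The point holds as a mismatch between the stated design and the named analyses, with a conditional consequence. If daily records are pooled and both pain and exposure cluster by person, naive standard errors are too small, by a factor of about 1.4 to 3.1 under the central assumptions (m = 60, pain ICC 0.3, exposure ICC 0.05 to 0.5). If exposure does not cluster, the loss is efficiency only.

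Clustering is plausible because the article itself distinguishes operators from passengers, and boat types, units and missions. Differing within- and between-person slopes are plausible because it names pre-existing pathology and under-reporting. Neither is demonstrated. Serial correlation and shared boat exposure were not modelled.

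**What to change.** In Statistical methods, state the unit of analysis and make the main analysis of daily VAS a participant-level mixed model, or a model with participant fixed effects. Split exposure into the person's own mean and the daily deviation from it, and read the acute effect from the within-person term. Use standard errors clustered by participant, allowing for boat and centre where crews share exposure.

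For pain yes/no, use conditional logit, or a mixed logit with the same split of exposure. Keep Pearson coefficients descriptive, or replace them with repeated-measures correlation.

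Do not add the previous day's VAS to the main model. It is correlated with a participant random intercept and can adjust away pain carried over from earlier exposure, while duration of pain is itself of interest. If carry-over matters, use lagged exposure terms.

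The cost is analysis wording; standard software suffices and no new data are needed. Intervals may widen if exposure clusters by person. Conditional logit drops participants whose pain status never varies; the mixed logit keeps them.

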**Figure 2 F2:**
[figure not shown]
On the left is a photograph of the MAREC device and related connections and on the right the kidney belt containing a three-axis accelerometer worn by the participating operators.

Accelerations will be analysed on all nine channels for the following characteristics:

*Number of impacts*: slamming impacts will be defined by the amplitude of the vertical accelerations measured on the boat hulls, where this peak acceleration exceeds 20 m/s^2^ or 2*g*. Peak accelerations below this level will not qualify as impacts relevant for analysis in this study.*Peak acceleration levels*: the peak acceleration value will be defined as the highest registered acceleration data point in each impact.*Range of rise times and correlation to peak acceleration levels*: rise time is defined as the time from nominal 0*g* to peak acceleration value.*Range of vector sum*: the force vectors will be the calculated vector sum resulting from the vertical force vector Z and the two horizontal force vectors X and Y. This value will be higher than any of the included three single-axis values and will show the magnitude of the total impact.*Three-dimensional impact measurement*: the direction and the acceleration of each impact will be recorded on the hull and on two boat operators per boat, using three-axis accelerometers.*Range of impact durations*: impact durations will be calculated as the time from the datapoint where the vertical acceleration exceeds 0*g* in each hull impact, exceeding 2*g* vertically until the last datapoint falls under 1.0*g*.*Range of jerk (speed of onset of impacts)*: the range of jerk, defined as the rate of the initial change of acceleration, will also be analysed. It is the derivative of the peak acceleration value (m/s^2^) divided by the time it took to reach it.^25^

Data output from the device will be presented in various graphic formats, for example, line graphs, allowing zooming from one full day of exposure down to showing the shape of a single impact regarding all characteristics of the impact (figure 3), or as histograms showing the numbers of impacts reaching different peak levels.^26^ To allow for a wide variety of analyses, all acceleration data will be stored in binary files as unfiltered raw data (figure 4). If a participating centre cannot use the MAREC data logger, another device with identical performance, sensors, software and output file format may be used.

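### The onboard versus off-boat self-control cannot show which impact characteristics are harmful, and the stated models compare those characteristics without it

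*Protocol article*

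**What the plan says.** The Introduction of the Protocol article gives as its second aim the types and magnitudes of impact that may be harmful. The study design section calls the study self-controlled, and the Pain section says how: "Participants will serve as their own controls by comparing periods of exposure onboard with periods of not working onboard". Pain is recorded on both kinds of day: "Participants will be urged to log pain daily for the whole test period, regardless of whether they have been on board a boat or not".

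The list of acceleration characteristics after Figure 2 defines a slamming impact by a vertical hull peak above 20 m/s² (2 g) and adds: "Peak accelerations below this level will not qualify as impacts relevant for analysis in this study". The other quantities belong to a single impact. For example, "rise time is defined as the time from nominal 0*g* to peak acceleration value".

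Under Statistical methods, "We will use Pearson correlation coefficients to examine the association between human impact exposure and pain scores". Linear regression follows, "controlling for potential confounding variables (eg, age, sex, body mass index"). ANOVA-based and logit models are then to "identify which characteristics of the impacts correlate to reported pain of various intensities, locations and durations after exposure". From these results the article intends to establish which exposure levels and characteristics are safe.

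**The concern.** The control condition and the second aim do not fit together. On a day without a qualifying impact, whether ashore or on a calm trip, there is no peak, rise time, duration, jerk or vector sum to relate to pain. Comparing onboard with off-boat periods therefore says whether exposure as a whole goes with more pain. It says nothing on whether a sharp impact is worse than a slow one. Number of impacts is the exception, because it is a true zero on those days.

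The analysis of characteristics must rest on differences among impact days. There the stated methods name no person term, so differences between people (habitual pain, role, boat, unit) mix with differences between days. A reader told that participants are their own controls would assume protection that this analysis lacks. The Discussion wants to use the results for training exposure limits and calibrated dashboard instruments, so a wrongly ranked characteristic could carry into practice.

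**Working it through.** The plan gives no figure for this point. Its sample size of 192 reproduces as 6 × 2 × (20 × (1.960 + 0.842)/14)² = 6 × 32.04 = 192.2, but it does not bear on the question. Only the pain SD of 20 mm is taken from there. All other inputs below are assumptions.

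**Step 1. What the self-control identifies.** Let A = 1 on a day with a qualifying impact and 0 otherwise, and let x be a per-impact characteristic, which exists only when A = 1. The difference in mean pain between A = 1 and A = 0 is one number per person, the net effect D. No function of D separates the effect of one x from another. This follows from the definitions alone.

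**Step 2. Impact days only, pooled over people.** Suppose x has no within-person effect on pain. Then pooled r = (person-level correlation) × √(between-person share of the variance of x × between-person share of the variance of pain). With an assumed person-level correlation of 0.3, simulation gave r = 0.15 pooled and 0.00 within person. By the formula, 0.15/0.3 = 0.5, which corresponds to half of each variance lying between people. The spurious r is 0 if the person-level correlation is 0, and with a correlation of 0.3 it cannot exceed 0.3.

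**Step 3. If impact-free days were scored 0 (not stated in the article).** Let π be the share of onboard days, with every onboard day taken to have an impact. Let μ and σ be the mean and SD of x onboard, CV = σ/μ, and b the slope in mm per SD. In units of σ:

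- cov(x₀, pain) = π(1 − π)D/CV + πb
- var(x₀) = π + π(1 − π)/CV²
- the sign of r reverses for b < 0 once D > |b| × CV/(1 − π)

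Assume π = 0.25, D = 5 mm and a residual pain SD of 20 mm. Let x be lognormal with log-SD 0.4 for rise time (CV 0.417), 0.25 for peak (CV 0.254) and 0.35 for duration (CV 0.361), independent of one another. Only rise time matters, with b = −4.

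- Rise time: cov = 0.1875 × 5/0.417 − 0.25 × 4 = 1.25; var(x₀) = 1.33; pain SD = √(400 + 0.25 × 16 + 0.1875 × 25) = 20.2; r = 1.25/(1.154 × 20.2) = +0.05. On onboard days the true r is −4/√416 = −0.20 (simulated −0.19).
- Peak and duration, with no true effect: r = +0.10 each, and r = 0.89 with each other. On onboard days all of these are 0.
- Reversal threshold: 4 × 0.417/0.75 = 2.2 mm for b = −4, and 1.1 mm for b = −2.

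| D (mm) | b (mm per SD) | r for rise time, zeros included |
|---|---|---|
| 2 | −4 | −0.004 |
| 3 | −4 | +0.02 |
| 5 | −4 | +0.05 |
| 10 | −4 | +0.15 |
| 10 | −2 | +0.17 |

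The threshold depends on the assumptions. For b = −2 and CV 0.3 it is 0.75, 1.0, 1.5 and 3.0 mm at π = 0.2, 0.4, 0.6 and 0.8. With CV 0.5 it runs from 1.25 to 5.0 mm.

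**Step 4. Joint model with zeros.** With all three characteristics in one linear regression, the rise-time coefficient keeps its negative sign for D = 3 to 10 mm and b = −2 and −4 (about −0.9 to −3.0 mm per SD). Peak and duration, which have no effect, still receive positive coefficients.

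**Step 5. Two-part coding.** With an onboard indicator plus centred characteristic terms, the Step 3 setting returns 4.97 mm for the indicator (truth 5) and −3.92 mm per SD for rise time (truth −4).

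**The case against.** The strongest reply is that the article contains no faulty rule. A reader might infer that off-boat days enter the characteristic models as zeros and that the plan would therefore report rise time with the wrong sign. The text does not support this. Zero-scoring appears nowhere, and coding of that kind is commonly left to a full protocol or analysis plan. The phrase on pain after exposure, and the stated intention to categorise impacts by their characteristics, fit an analysis of impact days only. Nor does the article say that the onboard versus off-boat contrast is what identifies the characteristics. Even with zeros, the sign reversal is confined to single-variable Pearson correlations above a threshold (Steps 3 and 4), and at D = 0 it does not occur.

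All of this stands, and it makes Step 3 a conditional hazard. It does not dispose of the main point. On the reading most favourable to the plan, impact days only, the characteristics can be compared, but across pooled people and without the self-control that the design section advertises. Age, sex and body mass index are given as examples of covariates. Adjusting for them does not replace a within-person comparison, and nothing under Statistical methods links the self-control to these models.

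**Conclusion.** The point holds in limited form, as a cheap improvement. The self-control estimates only the net effect of exposure. For per-impact characteristics the stated methods carry no onboard term and no person term, so the second aim is pursued without it. The size depends on how strongly exposure and habitual pain go together across people, which the article does not give: under an assumed person-level correlation of 0.3, a null characteristic shows r = 0.15 pooled against 0.00 within person.

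The distortion from zero-scoring applies only if that coding were used and if onboard and off-boat pain differ. It should be read as a reason to rule the coding out. It is not evidence that the plan adopts it. The onboard share, effects, slopes and distributions used here are all assumed.

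**What to change.** In Statistical methods, state a two-part exposure:

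1. An indicator for any qualifying impact that day, estimated within person against that person's impact-free days.
2. Terms for the per-impact characteristics (peak, rise time, duration and so on), centred on each person's own impact days and set to 0 on other days.

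Add that conclusions on which characteristics matter come only from the second part, and that no Pearson coefficient for a per-impact characteristic includes days without an impact. Number of impacts may keep its true zero.

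The cost is about two sentences and a recoding of the exposure variables, with no new data. The drawback is that characteristic effects rest on within-person variation among impact days, so their intervals will be wider.
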